### Participant withdrawal

A participant may be withdrawn from the trial by their clinician whenever continued participation is considered to no longer be in the participant’s best interests, but the reasons for doing so must be recorded. In these cases routine follow-up and safety data will be collected but not any further study-specific data.

A participant may withdraw from the trial at any point without impact on their ongoing care. No further data would be collected. However, data up to that point will be retained. Permission will be sought from patients wishing to withdraw to allow use of their routine follow-up data for trial purposes, especially safety data.

### Sample size

Thirty patients will be recruited from two sites, with 20 in the study drug (octreotide) arm and 10 in the placebo. This sample will allow us to demonstrate the feasibility of conducting a full-scale randomised trial. This study is not powered to detect differences in treatment effect but will obtain estimates of an effect and its variance.^30^ This sample size will allow us to estimate patient consent rate with a 95% CI of ± 10% (based on 100 participants approached). The secondary outcome data will provide the required information for a sample size calculation for the primary end point of a subsequent trial.^31^ Survival to discharge is above 96% for both study sites and hence it is likely that the ninety day follow data collection will be achieved for the majority of patients.

#### Recruitment rate

Over 275 patients per year will be eligible for study inclusion across the two study sites. With a 10 month recruitment period, this requires a 13% recruitment rate. A recent interventional trial in liver transplantation at the RFH achieved a 53% recruitment rate.^32^ Staff involvement and recruitment strategies will be similar in this study indicating this is a deliverable recruitment target.

### Data collection

Data will be collected on trial-specific electronic CRFs (eCRFs) and anonymised data collated on a secure central trial database (MACRO, Elsevier, Amsterdam, Netherlands) on a server in University College London (UCL). Physical trial material will be stored locally at each study site in a secure setting. A trial-specific data management standard operating procedure will contain details of the software to be used for the database, the process of database design, data entry, data quality checks, data queries, data security and database lock. At the end of the trial, all essential documentation will be archived securely for a minimum of 20 years from the declaration of the end of the trial.

All in-hospital data required for the study is part of routine medical care and as such is expected to have a high rate of completeness. Out-of-hospital data is similarly part of routine medical care. The completeness of study-specific PROM questionnaires performed before and after transplantation will be maximised through reminders by telephone and during clinic appointments.

Data will be analysed for completeness and accuracy through a check of 10% of patient records against the source data.

Third party data access will be assessed on a case-by-case basis by the Trial Management Group (TMG), approved by the TSC and limited specific anonymised data will be released, as appropriate. Patients will be consented for further analysis of anonymised data.

### Statistical methods

A statistical analysis plan will be approved by the TSC, prior to data analysis.

The following variables will be used to assess baseline comparability of the randomised groups:

Study centre at which transplant performed.Age.Sex.The model for end-stage liver disease score.^33^The UK end-stage liver disease score.^34^Aetiology of liver disease.The UK donor risk index.^35^Organ graft undergoing normothermic machine perfusion.Presence of portal hypertension.Severity of preoperative renal dysfunction (estimated glomerular filtration rate).American Society of Anesthesiologists score.Pr-operative haemoglobin level.EuroQol-5D-5L questionnaire scores.Liver disease Quality of Life questionnaire score.

Patients will be analysed according to the groups to which there were randomised.

#### Primary outcomes

The primary outcome feasibility measures will be quantified using numbers (%). The degree of precision will be quantified using exact 95% CIs.

#### Secondary outcomes

Numerical outcomes will be summarised using either mean (SD) or medians (IQR) as appropriate. Binary and ordinal outcomes will be summarised using number (%). The degree of precision will be quantified using 95% CIs. Differences between groups will be quantified using differences in means or proportions, as appropriate with corresponding 95% CIs.

Since this is a feasibility study, no formal statistical tests are planned.

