### Randomisation

Consented patients who proceed to transplantation will be randomised. Remote-site computerised random allocation will be performed with a centrally generated code (www.sealedenvelope.com) that will correlate with a coded syringe held in the secure study drug storage facility at each study centre. Patients will be stratified within the randomisation process by source of liver graft (brain death, DBD, or cardiac death donor, DCD) to ensure that patients are balanced for these factors across the two treatment groups. Patients will be randomly allocated to either the octreotide or placebo study groups in a 2:1 ratio. The randomisation list will be held centrally at a dedicated and independent off-site facility that will be contactable 24 hours a day.

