#### Secondary outcomes

A number of secondary outcome measures will be collected to help shape future trials in terms of assessing potential primary outcome measures and monitoring safety end points.

Intraoperative cell salvage volume (as a proxy for blood loss).Intraoperative urine output during each surgical phase.Mean arterial blood pressure during each surgical phase.Requirement for and mean vasopressor and/or inotrope infusion rate during each surgical phase.Volume or mass of de novo packed red blood cells and other clotting products during surgery and on the ICU (within first 24 hours, 72 hours and 1 week).Incidence of AKI as defined by the Acute Kidney Injury Network stage 1 criteria (a 50% increase in serum creatinine from baseline or less than 0.5 mL/kg/hours urine output for 6–12 hours post transplant) within 24 hours, 72 hours, 1 week.Incidence of postoperative RRT at 24 hours, 72 hours, 1 and 2 weeks postoperatively.Incidence of new or worsened CKD at 30 and 90 days.Mortality, early allograft dysfunction, graft loss and liver graft function at 30 and 90 days.Patient recorded outcome measures (PROM) preoperatively and at 90 days postoperatively;Liver Disease Quality of Life questionnaire.^28^EuroQOL-5D-5L questionnaire.^29^

Major safety outcomes will include:

Unexpected or resistant bradycardia,.Abnormal QTc interval (460 ms in men, 470 ms in women) or associated ventricular arrhythmia or Torsades de Pointes.Unexpected or resistant hypoglycaemia (blood sugar <4 mmol/L).Potential allergic or anaphylactic reaction to any medication.Any report of an abnormal response to codeine or morphine.Development of venous or arterial thrombosis.Cardiac event including acute coronary syndrome, new heart failure, arrhythmia or resuscitated cardiac arrest.

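### The 90-day PROM scores are compared by a simple difference in means; adjusting for the preoperative score and donor type would be a minor, conditional gain in precision

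*Protocol article*

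**What the plan says.** - **Estimator.** Statistical methods, Secondary outcomes: "Differences between groups will be quantified using differences in means or proportions, as appropriate with corresponding 95% CIs". No covariate or stratum is named, and no formal tests are planned.
- **Repeated measure.** Outcomes, Secondary outcomes, lists "Patient recorded outcome measures (PROM) preoperatively and at 90 days postoperatively", with LDQOL and EQ-5D-5L as the two instruments.
- **Stratification.** Randomisation: "Patients will be stratified within the randomisation process by source of liver graft (brain death, DBD, or cardiac death donor, DCD"). In the analysis, donor type returns only as an exploratory subgroup (Sensitivity and other planned analyses).
- **Baseline values.** Statistical methods lists 14 variables for judging whether the groups are comparable, including both questionnaire scores and "Severity of preoperative renal dysfunction (estimated glomerular filtration rate"). No other use of the preoperative scores is stated.
- **Purpose.** Sample size: "Thirty patients will be recruited from two sites, with 20 in the study drug (octreotide) arm and 10 in the placebo". And: "This study is not powered to detect differences in treatment effect but will obtain estimates of an effect and its variance". The same section says that the secondary outcome data will feed the sample size calculation of the next trial.
- **SAP.** One is to be approved by the steering committee before analysis; it is not shown.

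**The concern.** The sentence on differences names an estimator. Read with the baseline list and the subgroup paragraph, it describes a plain arm contrast. For the 90-day questionnaire scores the same score is already in hand from before surgery, and it is usually the best single predictor one could ask for. Leaving it out means that:

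1. any chance difference between 20 and 10 patients at baseline passes into the 90-day difference in proportion to the correlation;
2. the interval is wider than the data allow when that correlation is moderate or high;
3. the planned summaries (mean and SD or median and IQR, and the crude difference) contain neither the residual SD nor the baseline–90-day correlation. A definitive trial that adjusted for baseline would need one of these, because its required size scales with 1 − r².

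The third consequence bears most directly on the stated purpose of estimating an effect and its variance.

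**Working it through.** **The plan's own precision figure.** The only one stated is for consent: "This sample size will allow us to estimate patient consent rate with a 95% CI of ± 10% (based on 100 participants approached"). Half-width = 1.96 × √(p(1 − p)/100), which is 9.8 points at p = 0.5 and 9.0 at p = 0.3. It reproduces. No precision is stated for between-arm differences, so the rest is computed here.

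**Inputs from the protocol:** 20 octreotide, 10 placebo, N = 30. **Assumptions:** all 30 patients supply both scores; the baseline–90-day correlation r is unknown and varied from 0 to 0.7. In the simulation, 30% of grafts are DCD, and allocation is in permuted blocks of six at 2:1 within donor type.

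**Crude contrast.** SE = √(1/20 + 1/10) = √0.15 = 0.387 SD. The 95% half-width = t(28) × 0.387 = 0.79 SD.

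**Chance imbalance.** For an unstratified baseline variable, the between-arm difference has the same SE of 0.387 SD. P(|difference| > 0.5 SD) = 2 × [1 − Φ(0.5/0.387)] = 0.197, about 20% per variable.

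**Adjusted contrast.** With k covariates, the variance is multiplied by (1 − r²) × (1 + k/(N − k − 3)), and t(28) becomes t(28 − k). For k = 2 (baseline score plus a donor type that does not predict outcome), the second factor is 1 + 2/25 = 1.08. For r = 0.5: 0.75 × 1.08 = 0.81, √0.81 = 0.90, and the change in t brings the width ratio to 0.903.

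| r | Half-width, baseline only (SD) | Half-width, baseline + donor type (SD) | Width change, baseline + donor type |
|---|---|---|---|
| 0 | 0.81 | 0.83 | +4% |
| 0.3 | 0.77 | 0.79 | −0.5% |
| 0.5 | 0.70 | 0.72 | −10% |
| 0.7 | 0.58 | 0.59 | −25% |

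Break-even is at r of about 0.20 with one covariate and 0.28 with two.

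**Check by simulation** (8,000 trials per setting), ratio of adjusted to crude width:

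| Donor-type effect | r = 0 | r = 0.3 | r = 0.5 | r = 0.7 | Coverage of crude interval |
|---|---|---|---|---|---|
| 0 | 1.025 | 0.975 | 0.888 | 0.730 | about 95% |
| 0.5 SD | 0.996 | 0.951 | 0.864 | 0.713 | 95–96% |
| 1 SD | 0.930 | 0.885 | 0.804 | 0.663 | 96.5–97% |

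The formula treats donor type as unbalanced by design, so it slightly overstates the cost of including it. The simulation, with stratified allocation, gives a worst case of +2.5%. Hence the stated downside of 2–4%.

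**What the next trial would lose.** A baseline-adjusted trial needs (1 − r²) times the size implied by the crude SD: 0.75 at r = 0.5 and 0.51 at r = 0.7. The planned summaries do not allow that factor to be estimated.

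**The case against.** The strongest reply is that the plan is statistically sound and that the choice of covariates belongs in the SAP. Much of this stands.

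- **Adjustment is not ruled out.** The protocol never calls the difference unadjusted, and the unseen SAP may specify a model. The point therefore rests on the estimator that the protocol states, not on an omission. An SAP that followed the text literally would be crude.
- **A reader might infer that the crude analysis is biased or its interval invalid.** It is neither. Over randomisation the estimate is unbiased, and simulated coverage is about 95–97%: nominal or somewhat conservative.
- **A reader might infer that donor type is neglected.** It is roughly balanced by stratification and examined as a subgroup. The imbalance argument applies to unstratified variables.
- **A reader might extend the point to the renal outcomes through baseline eGFR.** AKI, renal replacement therapy and new or worsened CKD are incidences. A linear eGFR adjustment does not fit them, and modelling with 10 controls would be unstable. The AKI and CKD definitions already refer partly to baseline renal status.
- **A reader might want a donor-stratified risk difference for binary outcomes.** With 30% DCD there would be about three DCD controls (0.30 × 10), and no gain has been shown.
- **The gain is conditional.** The protocol gives no correlation, and below about 0.2–0.3 there is no benefit.
- **A correlation from 30 patients is imprecise.** An observed 0.5 has a 95% interval of about 0.17 to 0.73 (Fisher: atanh 0.5 ± 1.96/√27). It should be reported with that uncertainty. It is still more use to planners than no estimate.

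What survives is the case for the two questionnaires, which are measured at both times.

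**Conclusion.** The point holds in a limited form. For the 90-day LDQOL and EQ-5D-5L scores, the stated difference in means is valid but leaves out a preoperative measurement already collected and the stratification factor. Adjusting for both changes the interval width by about −10% at r = 0.5, −25% at r = 0.7, almost nothing at r = 0.3, and +2–4% if neither covariate is prognostic. These figures assume 30 complete pairs of scores and, for donor type, the simulated 30% DCD share and block size. Adjustment would also remove the part of a chance baseline difference that carries into the outcome, and would yield the residual SD and correlation for the definitive trial.

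The consequence is small. The primary outcomes are feasibility proportions and are untouched, no tests are planned, and the study is not powered for treatment effect. The crude SDs and event rates still support a conventional sample size calculation. This is a minor improvement, not a defect that threatens the study's conclusions.

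**What to change.** State the following in the SAP, before analysis:

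- **90-day LDQOL and EQ-5D-5L scores:** estimate the between-arm difference from a linear model with arm, preoperative score and donor type. Report the adjusted difference with its 95% CI, the residual SD, and the baseline–90-day correlation with its CI.
- **Other numerical outcomes:** include donor type only.
- **Binary outcomes:** leave as crude differences in proportions with 95% CIs. Do not add eGFR adjustment.
- **Crude summaries:** keep them by arm as description.

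The cost is a few lines of SAP text and code and no new data. Statistically it is two degrees of freedom for the questionnaire scores and one for the other numerical outcomes. If the covariates predict nothing, the interval is about 2–4% wider with both terms and about 2% wider with one.

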#### Sensitivity and other planned analyses

No sensitivity analyses are planned. There will be no interim analysis.

We will perform exploratory subgroup analyses for donor organ type (DCD and DBD), the presence of CKD and known portal thrombosis (or if diagnosed at transplantation). We will also assess the impact of surgical approach (cross-clamp vs any other approach), the use of machine perfusion vs cold storage and hospital site.

#### Patient replacement

Patients who are randomised and allocated to a treatment arm but subsequently do not complete the trial will not be replaced.

### Monitoring

#### Oversight committees

A TMG and TSC have been formed. The terms of reference and functions of these committees are provided in online supplemental appendix 4.

10.1136/bmjopen-2021-055864.supp4Supplementary data

The TMG will include the Chief Investigators, coinvestigators, trial staff, patient expert and study site principle investigators. The TMG will be responsible for overseeing the trial. The TMG will review recruitment figures, SAEs and substantial amendments to the protocol prior to submission to the Research Ethics Committee (REC).

#### Data monitoring

The TSC will represent a combined TSC and Data Monitoring Committee with expertise in performing and reporting clinical trials, statistical methods and clinical expertise for evaluation of post-transplant complications. The role of the TSC is to provide oversight for the trial and provide advice through its independent Chair to the Chief Investigator, the TMG, trial Sponsor, Funder, and host institutions on all aspects of the trial. The TSC will recommend any appropriate amendments/actions for the trial as necessary. The TSC is independent of the TMG, Funder and Sponsor and members have declared no competing interests.

#### Early stopping guidelines

The trial may be stopped before completion either on the recommendation of the TSC or the sponsor and chief investigator. There will be no statistical stopping rules.

#### Adverse events

All adverse events will be recorded in the medical records in the first instance. All SAEs within 90 days of patient enrolment will be recorded in the eCRF with clinical symptoms, a brief description and date of the event. SAEs will be reported to the Sponsor within 24 hours. Where the event is unexpected and thought to be related to the intervention, this will be reported to the Health Research Authority within 15 days. Participants suffering an SAE will be followed up until clinical recovery is complete and laboratory results have returned to expected values, or until the event has stabilised. Follow-up will continue after completion of trial follow-up if necessary. For the purpose of analysis, SAEs prior to discharge, within 30 days and within 90 days of enrolment will be analysed and published.

The sponsor will notify the REC and Medicines and Healthcare products Regulatory Agency (MHRA) of all SUSARs within 15 days. SUSARs that are fatal or life threatening will be notified to the MHRA and REC within 7 days of the sponsor learning of them.

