**Methods and analysis:**

We describe a multicentre, double-blind, randomised, placebo-controlled feasibility study of continuous infusion of octreotide during liver transplantation surgery. We will recruit 30 adult patients at two liver transplant centres. A blinded infusion during surgery will be administered in a 2:1 ratio of octreotide:placebo. The primary outcomes will determine the feasibility of this study design. These include the recruitment ratio, correct administration of blinded study intervention, adverse event rates, patient and clinician enrolment refusal and completion of data collection. Secondary outcome measures of efficacy and safety will help shape future trials by assessing potential primary outcome measures and monitoring safety end points. No formal statistical tests are planned. This manuscript represents study protocol number 1.3, dated 2 June 2021.

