Key inclusion and exclusion criteria	Ages eligible for study: ≥18 years Sexes eligible for study: both Accepts healthy volunteers: no
	Inclusion criteria: adults aged 18 years and over undergoing primary liver transplantation of a whole or partial liver graft from a cardiac or brain dead donor
	Exclusion criteria: previous solid organ transplant, acute liver failure, fulminant hepatic failure, patients receiving a living donor liver graft, patients currently admitted to ICU prior to transplantation, requirement of haemodialysis or continuous veno-venous haemofiltration (CVVHF) preoperatively, known allergy or adverse reaction to octreotide, preoperative decision to use intra-operative CVVHF, a positive pregnancy test.
Study type	Interventional
	Allocation: patients will be randomised in a 2:1 ratio to either octreotide or placebo groups. Stratified randomisation of patients by source of liver graft (brain death or cardiac death). Masking: quadruple (participant, care provider, investigator, outcomes assessor)
	Primary purpose: feasibility
	Phase II
Date of first enrolment	July 2021
Target sample size	30
Recruitment status	Pending recruitment
Primary outcome(s)	Trial feasibility
Key secondary outcomes	Incidence of acute kidney injury Postoperative incidence of a new requirement for renal replacement therapy Incidence of new chronic kidney disease or deterioration of chronic kidney disease Incidence of early allograft dysfunction Patient mortality Intra-operative red blood cell salvage Volume of packed red blood cell transfusion administered Incidence of adverse events secondary to study drug infusion PROMs data

ICU, intensive care unit; PROMs, patient recorded outcome measures.

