### Outcomes

#### Primary outcome

The primary outcomes for this study are based on determining the feasibility of conducting an RCT of octreotide versus placebo infusion during liver transplantation. The feasibility will be assessed by:

Recruitment ratio (percentage of eligible patients undergoing transplantation who provide consent, target: ≥30%).Percentage of eligible patients who receive the study drug infusion in a blinded manner (target: ≥80% of patients).Incidence of drug-related serious unexpected adverse events (target: ≤20%).Completion of follow-up data collection (target: ≥90% patients).Patient refusal to enrol in study on admission for transplantation (target: ≤15%).Clinician refusal for inclusion or randomisation following patient recruitment (target: ≤15%).

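### Only serious adverse events are named for the eCRF and for analysis, so Table 1's secondary outcome of infusion-related adverse events of any severity is only partly captured

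*Protocol article*

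**What the plan says.** Five places in the protocol article deal with adverse events as data.

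- **Monitoring, Adverse events.** "All adverse events will be recorded in the medical records in the first instance". The next sentence is about serious events only: "All SAEs within 90 days of patient enrolment will be recorded in the eCRF", with symptoms, a short description and a date. The analysis sentence is also limited to serious events: "For the purpose of analysis, SAEs prior to discharge, within 30 days and within 90 days of enrolment will be analysed and published".
- **Trial design, Table 1, key secondary outcomes.** "Incidence of adverse events secondary to study drug infusion". Seriousness is not a condition; attribution to the infusion is.
- **Outcomes, Primary outcome.** "Incidence of drug-related serious unexpected adverse events (target: ≤20" (per cent). This measure is limited to events that are serious, unexpected and drug-related.
- **Outcomes, Secondary outcomes.** The section opens with its purpose: "A number of secondary outcome measures will be collected to help shape future trials in terms of assessing potential primary outcome measures and monitoring safety" (that is, safety endpoints). The list ends with seven major safety items: bradycardia (if unexpected or resistant), QTc prolongation or related arrhythmia, hypoglycaemia (if unexpected or resistant), possible allergic reaction, abnormal response to codeine or morphine, thrombosis, and cardiac events.
- **Abstract, Methods and analysis.** The primary outcomes are summarised as including "correct administration of blinded study intervention, adverse event rates", with no qualifier.

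Two other sections bear on capture. Data collection gives the general rule that trial data go on eCRFs and into the central database. Overdose sends overdoses and departures from the infusion schedule to the CRF whether or not a serious event follows.

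**The concern.** The rule for recording and analysing adverse events is narrower than one of the outcomes it has to supply. Table 1 needs every event attributed to the infusion. The Adverse events section carries forward only the serious ones.

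The gap matters because the trial is meant to inform the next one on safety. The Risks section says that octreotide's side effects in this setting are not known, and it faults earlier studies for not comparing or not assessing adverse events. If the tabulated result is SAEs plus seven chosen items, a reader may take it as the full incidence of infusion-related events. The next trial's tolerability and monitoring assumptions would then start too low.

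**Working it through.** The plan states no figure to reproduce. The check is to trace each adverse-event outcome to the route by which its data reach the database and the analysis.

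| Outcome or event | Where defined | Stated route to the eCRF | Stated analysis |
|---|---|---|---|
| Drug-related, serious, unexpected events | Primary outcome | Yes: a subset of SAEs | Yes |
| All SAEs to 90 days | Adverse events | Yes | Yes: three time points |
| Seven major safety items, serious or not | Secondary outcomes | Yes, through the general rule in Data collection | Yes, as secondary outcomes |
| Overdose or schedule deviation | Overdose | Yes | Not specified |
| Non-serious hyperglycaemia | Named as a risk in the Abstract; not among the seven items | None stated | None stated |
| Bradycardia neither unexpected nor resistant, and not serious | Outside the bradycardia item | Unclear: the cardiac-event item includes arrhythmia and might take it in | Unclear |
| Any other non-serious event attributed to the infusion | Table 1 outcome only | None stated | None stated |

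**Step 1, coverage.** The Table 1 outcome needs the union of all rows, restricted to related events. The first four rows have a route. Non-serious hyperglycaemia and other non-serious related events do not. Hyperglycaemia is the clearest example: the Abstract names both high and low blood sugar as risks, the Risks section counts blood sugar changes among the common ones, and the safety list carries only the low side.

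**Step 2, attribution.** The Table 1 outcome depends on a judgement that the event was due to the infusion. The Adverse events section mentions relatedness only for expedited reporting of unexpected events, and the eCRF content it describes has no relatedness entry. The seven safety items are defined by whether they occur, not by cause. Even for captured non-serious items, the article therefore does not say how they become related events.

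**Step 3, size.** The documents give no rate of non-serious related events, so the number missed is unknown. What one miss does to the result follows from the planned arms in Sample size (20 octreotide, 10 placebo):

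- octreotide: 1/20 = 5 percentage points per patient whose only related event is missed;
- placebo: 1/10 = 10 percentage points per such patient.

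As assumed values, 1, 2 or 4 such octreotide patients would lower the reported incidence by 5, 10 or 20 points (1/20, 2/20, 4/20). With none, nothing is lost. Within each arm the error can only be downward. The between-arm difference (octreotide minus placebo) could move either way: down 5 points for each octreotide patient missed, up 10 for each placebo patient missed.

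**The case against.** The strongest case on the other side has four parts.

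1. **Non-serious safety data do reach the database.** A reader might infer that nothing but SAEs enters the eCRF and that the Table 1 outcome cannot be computed at all. The documents do not support that. Secondary outcomes, Data collection and Overdose together provide for seven items that need not be serious, and for overdoses. This stands, and it limits the point to partial capture.

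2. **The Abstract is shorthand.** A reader might also infer that its adverse event rates, listed among the primary outcomes, cannot be obtained. They most plausibly abbreviate the Primary outcome measure, which is confined to serious events and can be taken from SAE data. This stands. What remains there is a difference in wording.

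3. **Table 1 is a one-line registry summary, and the safety list is its working definition.** This is possible, but the article does not say so, and the two differ in kind: one is defined by cause, the other by a fixed list of occurrences. If the list is the intended definition, Table 1 should say so, and the missing hyperglycaemia item would still need attention.

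4. **An article leaves eCRF detail to the full protocol, and the wording on medical records implies a later step.** Nothing states that non-serious events are barred from the eCRF, and a later transcription step may exist. That answers silence. It does not answer an explicit analysis sentence confined to SAEs beside an outcome that is not.

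It is also fair that collecting SAEs plus prespecified events is a defensible choice where, by the Introduction's figure, 70% of patients have complications. The outcome then has to be worded to match that choice.

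**Conclusion.** The point holds as an inconsistency of scope with a real but limited effect on the data. The stated rule for eCRF entry and analysis covers serious events, the safety list adds seven items, and the Table 1 outcome is wider than both. Non-serious hyperglycaemia and other non-serious events attributed to the infusion have no stated route, and no relatedness judgement is stated for non-serious events. Followed as written, the plan would understate infusion-related events by an amount the documents do not allow one to estimate, beyond 5 or 10 percentage points per affected patient by arm.

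The primary feasibility criterion on drug-related serious unexpected events is not affected. The conclusion assumes that the full protocol, which is not shown, has no wider adverse event log. If it has one, only the article's wording needs correcting.

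**What to change.** Amend the Adverse events section so that the eCRF also takes:

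- non-serious adverse events that the blinded investigator judges related to the infusion;
- hyperglycaemia, as a prespecified safety item beside hypoglycaemia, with a definition set by the clinical team.

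Record seriousness and relatedness for each, over a stated perioperative window. Seventy-two hours is one option, since Secondary outcomes already uses it for transfusion, kidney injury and renal replacement; the documents do not require it. SAE recording to 90 days stays as it is.

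Extend the analysis sentence so that the Table 1 outcome is reported by arm from these fields. Then align the wording of the Abstract, Table 1, Primary outcome, Secondary outcomes and Adverse events, so that each says whether it means serious, related, unexpected or all events. If the sponsor prefers SAEs plus listed items only, Table 1 should be narrowed to say so.

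The cost is a small amount of extra data entry for 30 patients, mostly from inpatient notes already being written, plus one blinded judgement per event.
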